### Statistical analysis

The statistical analysis will be conducted by a statistician of the Beijing Bozhiyin Science and Technology Co. Ltd, China. They are blinded to the whole trial and using Statistical Analysis System (SAS, Cary, NC, USA) version 9.2 and Statistic Package for Social Science (SPSS, Chicago, IL, USA) version 17.0 software packages. All mechanism, efficacy and safety analyses will be strictly conducted according to the intention-to-treat (ITT) principle and the full analysis set (FAS) population, the per-protocol set (PPS) population and the safety set (SS) population. Missing values will be replaced by the last observation carried forward (LOCF) method.

The statistical significance is defined as a two-sided *P*-value of <0.05 and 95% confidence interval. For descriptive statistics, continuous variables will be described as numerous, mean ± standard deviation, median, Q1 to Q3 and mini-maxi and dichotomous data will be reported as frequency and percentage. Baseline differences among the groups will be assessed with the use of Student’s *t*-test for normally distributed continuous variables and the non-parametric Mann-Whitney *U*-test for non-normally distributed variables. Comparisons between groups will be conducted by using an analysis of covariance (ANCOVA) with baseline as covariate. For efficacy analysis, changes from baseline to endpoint of treatment in scores will be tested with repeated measure analysis of variance (ANOVA). Within group differences will be assessed with paired *t*-test for normally distributed data and Wilcoxon signed-rank test for non-normally distributed data. Mechanism will be assessed between mechanism index and primary outcomes by ANCOVA and regression analysis. Safety will be assessed by participant compliance and adverse events. The endpoint events will be listed by detailed account.

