### Handling of withdrawal and dropout

Voluntarily withdrawalLoss of follow-upPoor compliance and presence of severe adverse effectsRevealing and uncovering blind in urgencyMisdiagnosisUsing forbidden drugs or treatments in the course of the trialTaking no medication during the trialNo evaluable records after medication

Reasons for withdrawing participants will be recorded in CRFs, and the last data would be included in data analysis.

The whole research plan would be terminated for the following circumstances:Occurrence of serious adverse events related to the research medicationFlawed protocolFunding and management problem due to the sponsorsAdministrative authorities terminate the trial

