#### Endpoint outcomes

Death incident: cardiovascular death, cerebrovascular death, sudden death, other cause of death.

Cardiovascular incident: unstable angina pectoris hospitalization, acute myocardial infarction, malignant arrhythmia, cardiac shock, revascularization and other cardiovascular incident.

Non-cardiovascular incident: stroke, pulmonary embolism, peripheral vessel, tumor, other non-cardiovascular incident.

All three groups will undergo a twelve-week treatment and two-week follow-up. Four visits in sum will be scheduled for each subject: one visit each in week 0, week 4, week 12 and week 14. The CRFs contains a range of information and this will be completed by the corresponding researchers at each center. Trial coordinators and therapists at each center will record above endpoint outcome and the details of these events throughout the treatment and follow-up period. Outcomes to be measured and the time points of data collection can be found in Additional file 1: Table S1.

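### LOCF is the only stated rule for missing values; with no visit between weeks 4 and 12, it can bias the week-12 comparison in either direction if outcomes are still changing

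*Protocol article*

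**What the plan says.** The Statistical analysis section states the rule without qualification: "Missing values will be replaced by the last observation carried forward (LOCF) method". It is not limited by outcome, by reason for missingness or by analysis set, and no alternative or sensitivity method is named. The section on withdrawal and dropout agrees: for those who leave, "the last data would be included in data analysis".

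The schedule under Endpoint outcomes is "one visit each in week 0, week 4, week 12 and week 14", with treatment ending at week 12. The efficacy analysis concerns change from baseline to the end of treatment, by repeated-measures ANOVA. Separately, "Comparisons between groups will be conducted by using an analysis of covariance (ANCOVA) with baseline as covariate".

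The sample size section allows for 15% dropout overall and assumes response rates of 60% on placebo, 88.5% in Group 1 and 82.5% in Group 2. The listed withdrawal reasons include poor compliance, severe adverse effects, emergency unblinding and use of forbidden treatments.

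**The concern.** LOCF assumes that a participant's angina would have stayed where it was at the last visit. Here that visit can be far from the time point analysed. Someone lost before week 4 has only the baseline value and so contributes zero change at week 12. Someone lost between weeks 4 and 12 contributes a value up to eight weeks old.

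If participants are still improving, each carried value understates the improvement. When one arm loses more participants, or loses them earlier, that understatement does not cancel between arms, and part of the week-12 difference comes from dropout and not from treatment. Several of the listed withdrawal reasons could plausibly differ between herbal and placebo arms. The rule governs all three primary outcomes, and the article states it outright, so this is not a detail left to an unseen analysis plan.

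**Working it through.** **Figures in the article.** The pooled two-sided chi-square formula without continuity correction gives 36 and 63 per group against the stated 37 and 64, within one of each. Then 64/0.85 = 75.3, so 76, which the article rounds up to 80. At 15% dropout, 0.15 × 80 = 12 participants per arm, or 36 of 240, would have carried values if all left before week 12.

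**Assumed inputs (not in the article).** SD 2; correlation 0.6 between visits; every arm improves by m4 = 1 unit by week 4 and m12 = 2 by week 12; a share e = 1/3 of dropouts leaves before week 4 and the rest between weeks 4 and 12. Dropout by arm is varied.

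**Formula.** Improvement lost per dropout: L = e × m12 + (1 − e) × (m12 − m4). With the inputs above, L = 1/3 × 2 + 2/3 × 1 = 1.33. With no true effect, the spurious difference in favour of treatment is (d_control − d_treated) × L.

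**No true effect.** Type I error comes from simulating ANCOVA on LOCF week-12 values, 80 per arm, two-sided 5%, 20,000 trials per row.

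| Dropout, treated vs control | Spurious difference | Type I error |
|---|---|---|
| 15% vs 15% | 0 | 5.0% |
| 12.5% vs 17.5% | 0.05 × 1.33 = 0.07 for treatment | 5.8% |
| 10% vs 20% | 0.10 × 1.33 = 0.13 for treatment | 7.8% |
| 20% vs 10% | 0.13 against treatment | 8.1%, of which 7.4 points favour control |
| 7.5% vs 22.5% | 0.15 × 1.33 = 0.20 for treatment | 11.8% |

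**Sensitivity to the time course, at 10% vs 20%.**
- No change over time: L = 0, bias 0, type I error 5.1%.
- Improvement of 0.5 then 1 unit: L = 0.67, bias 0.07, 5.8%.
- Most improvement early (1.7 of 2 units by week 4): L = 1/3 × 2 + 2/3 × 0.3 = 0.87, bias 0.09, 6.2%.
- Steeper (1.5 then 3 units): L = 2.0, bias 0.20, about 11 to 12%; at 7.5% vs 22.5% the bias is 0.30 and the error about 19%.

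**True effect of 1.0 at week 12, half of it by week 4.** The treated arm then improves by 1.5 and 3 units, so its L = 1/3 × 3 + 2/3 × 1.5 = 2.0. Expected estimate = 1.0 + d_control × 1.33 − d_treated × 2.0:
- 15% in both arms: 1.0 + 0.20 − 0.30 = 0.90.
- 20% treated, 10% control: 1.0 + 0.13 − 0.40 = 0.73 (0.73 to 0.74 in simulation).
- 10% treated, 20% control: 1.0 + 0.27 − 0.20 = 1.07.

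**On the article's response scale.** Take equal 15% dropout and let f be the share of each arm's final response rate already reached in the carried values. The planned 22.5-point difference for Group 2 becomes 22.5 × (0.85 + 0.15f): 19.1 points at f = 0 and 20.8 at f = 0.5. Power at 80 per group is then about 70% and 80%, against 83% for 68 completers per group.

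**The case against.** A reader might infer that LOCF will manufacture a benefit for the herbal granules. The documents do not support that. They give one overall dropout figure with no split by arm or time, so the unequal splits above are assumptions. If adverse effects drive withdrawal, the active arms may lose more, and LOCF then works against treatment. With equal dropout and no true effect the average bias is zero. In that scenario the simulated error is also nominal, so treating carried values as observed did not by itself inflate it.

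Nor does every dropout carry an early value: someone lost after week 12 has a genuine week-12 result. Data-collection times are in an additional table that is not shown, so an early-termination assessment cannot be ruled out; the article states none.

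The 60% placebo response implies improvement over time but says nothing about how much occurs between weeks 4 and 12. Under milder inputs the error is only about 6%. A per-protocol analysis is also planned. It is a partial check, because it conditions on completing and complying.

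All of this stands and limits the claim. It does not rescue LOCF as the sole rule: the dropout pattern cannot be known in advance, and the method is not reliably conservative.

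**Conclusion.** The concern holds in conditional form. The article fixes LOCF as its only missing-data rule, on a schedule where those lost before week 12 are represented by week-0 or week-4 values. Bias in the week-12 comparison needs outcomes that change after the last visit, together with either dropout that differs between arms in amount or timing, or a true effect to dilute. Its direction is not fixed.

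Across the scenarios examined, type I error runs from nominal to about 12% under the central time course and to about 19% under the steeper one. A true effect of 1.0 is estimated at between 0.73 and 1.07. These sizes depend on the assumed SD, correlation, time course and dropout split. What the text says is certain; a false effect in this trial is only a possibility. The rule should be changed, but it does not invalidate the design.

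**What to change.** Replace LOCF as the primary rule.

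- For continuous outcomes such as the SAQ dimension, use a likelihood-based mixed model for repeated measures on the observed data, with baseline, arm, visit and arm-by-visit terms and the week-12 contrast as the primary result.
- For attack frequency and nitroglycerin use, apply a repeated-measures model suited to counts, on observed data. Include an offset for days observed only if those days are recorded; the article does not say that they are.
- Add control-based multiple imputation as a sensitivity analysis, and keep LOCF only as a further one.

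The cost is revised wording and a little more programming in the SAS package already named. No new data are needed unless the count offset is wanted and observation days are not being captured. The new primary analysis relies on a missing-at-random assumption, which is why the control-based sensitivity analysis belongs beside it. Recruitment was ongoing when the article was submitted; the change should be made and dated before unblinding.

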**Methods/Design:**

This is a north-east Chinese, multi-center, multi-blinded, placebo-controlled and superiority randomized trail. A total of 240 patients with stable angina pectoris will be randomly assigned to three groups: two treatment groups and a control group. The treatment groups will receive Chinese herbal medicine consisting of *Yi-Qi-Jian-Pi* and *Qu-Tan-Hua-Zhuo* granule and *Yi-Qi-Jian-Pi* and *Qu-Tan-Hua-Yu* granule, respectively, and conventional medicine. The control group will receive placebo medicine in addition to conventional medicine. All 3 groups will undergo a 12-week treatment and 2-week follow-up. Four visits in sum will be scheduled for each subject: 1 visit each in week 0, week 4, week 12 and week 14. The primary outcomes include: the frequency of angina pectoris attack; the dosage of nitroglycerin; body limited dimension of Seattle Angina Questionnaire. The secondary outcomes include: except for the body limited dimension of SAQ, traditional Chinese medicine pattern questionnaire and so on. Therapeutic mechanism outcomes, safety outcomes and endpoint outcomes will be also assessed.

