## Methods/Design

### Study design

This is a north-east Chinese, multi-center, multi-blinded, placebo-controlled and superiority randomized trail with three parallel groups. The study protocol was based on strict and scientific recommendations in the Consolidated Standards of Reporting Trials (CONSORT) statement [15] and SPIRIT 2013 Statement [16]. This trial was supported financially by the National Basic Research Program of China ‘973 Program’ (Number 2013CB531704). The trial was registered in Chinese ClinicalTrials.gov with approval number ChiCTR-TRC-13003608.

Two hundred and forty participants will be recruited at six large comprehensive hospitals in China, which are: Affiliated Hospital of Liaoning University of TCM, Liaoning Institute of Chinese Medicine, Affiliated Hospital of Inner Mongolia National University, Shen-Zhou Hospital of Shenyang Medical College, First Affiliated Hospital of China Medical University, and Sheng-Jing Hospital of China Medical University. After a two-week run-in period, eligible subjects will be randomly assigned to one of 3 groups, *Yi-Qi-Jian-Pi* and *Qu-Tan-Hua-Zhuo* group (Group 1), *Yi-Qi-Jian-Pi* and Qu-Tan-Hua-Yu group (Group 2), and the placebo group. All three groups then underwent a 12-week treatment and a 2-week follow-up period. The flow chart is listed in Figure 1.

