**Trial flow chart.**

### Randomization and allocation concealment

A total of 240 patients will be randomly assigned in a ratio of 1:1:1 using the statistical package. To guarantee rigorous methodology, stratified block randomization and central coordination will be initiated. The unique code will be assigned to each newly eligible participant and properly preserved in the trial management board. This procedure ensures each eligible patient having an equal probability of being assigned to three different groups, which will not be influenced by the researchers. A statistician expert of the Beijing Bozhiyin Science and Technology Co. Ltd, Beijing, China will act as the coder and they will be shielded from patient recruitment.

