### Outcomes

#### Efficacy outcomes

The primary outcomes include:Frequency of angina pectoris attacksDosage of nitroglycerinBody limited dimension of Seattle Angina Questionnaire (SAQ)

The secondary outcomes include:SAQ except for the body limited dimensionTCM pattern questionnaireThe duration of angina pectorisAngina pain severity

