### Sample size calculation

According to the response rates of treatment, Group 1 and placebo were 88.5% and 60%, respectively; 37 patients of each group was estimated as sufficient to achieve 80% power in detecting treatment differences, based on two-sided Chi-square test without continuity correction at a significance level of 0.05 (α = 0.05; 1-β = 0.80). In the same way, assuming the clinical effective rates of Group 2 and placebo were 82.5% and 60%, respectively and 64 patients of each group was estimated as sufficient to achieve 80% power. Meanwhile, taking into account a dropout of 15%, we concluded that a total of 240 patients with 80 for each group would need to be recruited to ensure statistically significant results.

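### Three unranked primary outcomes and two herb-versus-placebo comparisons are all judged at an unadjusted two-sided 0.05, with no rule for what counts as success

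*Protocol article*

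**What the plan says.** The Abstract and the Efficacy outcomes section give the same three primary outcomes, in the Abstract's words: "The primary outcomes include: the frequency of angina pectoris attack; the dosage of nitroglycerin; body limited dimension of Seattle Angina Questionnaire". Neither place ranks them or says how many must be positive.

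Study design describes a "placebo-controlled and superiority randomized trail with three parallel groups", and allocation is 1:1:1 with 240 patients in total.

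Sample size calculation handles the two herb arms separately. For the first it states that response in "Group 1 and placebo were 88.5% and 60%, respectively; 37 patients of each group was estimated as sufficient", "based on two-sided Chi-square test without continuity correction at a significance level of 0.05". It then treats Group 2 (82.5% against 60%, 64 per group) in the same manner. Alpha is not divided between the two comparisons.

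Statistical analysis has one significance rule for everything: "The statistical significance is defined as a two-sided *P*-value of <0.05 and 95% confidence interval". Between-group comparisons are by ANCOVA adjusted for baseline, and changes in scores are tested by repeated-measures ANOVA. No hierarchy, gatekeeping or adjustment is mentioned.

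**The concern.** Three outcomes and two comparisons with placebo make six primary tests. The article does not say which of them carries the conclusion. The sample size does not settle this, because it rests on a response rate that is not one of the three primary outcomes.

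Two things are at stake. If any one of the six may support a claim, the overall error is well above the stated 5%. And because the success rule is open, it could be chosen after the results are known. That would weaken a trial which its Discussion presents as a source of high-quality evidence.

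**Working it through.** **Inputs from the protocol article.** Two-sided 0.05 and 80% power; response rates 88.5%, 82.5% and 60%; 37, 64 and finally 80 per group; 15% dropout (Sample size calculation). Three arms, 1:1:1 (Study design; Randomization and allocation concealment). Three primary outcomes (Efficacy outcomes).

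**Assumed.** The correlation ρ between the three outcomes is not in the document, so a range from 0 to 0.7 is shown.

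**1. The plan's own sample size.** For two proportions with pooled variance and no continuity correction,

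n = [1.960·√(2p̄(1−p̄)) + 0.842·√(p₁(1−p₁)+p₀(1−p₀))]² / (p₁−p₀)².

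- Group 1: p̄ = 0.7425, so n = (1.212 + 0.492)² / 0.285² = 35.7, or 36. The article states 37.
- Group 2: p̄ = 0.7125, so n = (1.255 + 0.522)² / 0.225² = 62.3, or 63. The article states 64.

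Both agree to within one patient, and only with the full two-sided 0.05 spent on each comparison. At 0.025 each, the same formula needs 44 and 76. So the design calculation spends 0.05 twice. Dropout: 64 / 0.85 = 75.3, or 76, which the article rounds up to 80.

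**2. Overall error if any one significant result suffices.** Six independent tests would give 1 − 0.95⁶ = 26.5%. That is too high, because the two comparisons share the placebo arm (correlation 0.5 between their test statistics) and the outcomes are correlated. A simulation allows for both: 1,000,000 draws with no effect anywhere, normal test statistics and three equal arms. A test rejects when |z| > 1.96.

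| ρ between outcomes | Any rejection, either direction, 6 tests | Herb better than placebo, 6 tests |
|---|---|---|
| 0 | 24.8% | 13.0% |
| 0.3 | 23.8% | 12.1% |
| 0.5 | 21.9% | 11.0% |
| 0.7 | 19.2% | 9.6% |

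The nominal rates for a single test are 5% and 2.5%. One outcome with two comparisons gives about 9% in either direction.

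**3. If all three outcomes must succeed within a comparison.** The chance that either herb arm falsely passes on all three, counting both directions, is about 0.03% at ρ = 0, 0.6% at 0.5, 1.7% at 0.7 and 4.2% at 0.9. The unstated success rule therefore moves the error from below 5% to around 20%.

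**4. Power after adjustment, on the article's response rates.** With 80 × 0.85 = 68 evaluable per arm, by binomial simulation:

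| Procedure for the two comparisons | Group 2 power |
|---|---|
| Unadjusted 0.05 each | 84.0% |
| Holm | 83.5% |
| Fixed order, Group 1 then Group 2 | 83.1% |
| Bonferroni, 0.025 each | 76.1% |

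Group 1 power is 97.8% unadjusted and 96.6% under Holm.

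**The case against.** **Detail left to an analysis plan.** A condensed article may leave the multiplicity procedure to a document not shown, and a general threshold does not rule out a hierarchy. This is fair as far as it goes. But the article is not silent: it fixes an unsplit 0.05 in the design calculation and again in the analysis, and the choice and ranking of primary outcomes belong to the protocol.

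**The decision rule is inferred.** Nowhere does the article say that one positive result is enough. ANCOVA and repeated-measures ANOVA are not spelled out as six ungated pairwise tests. An overall three-group test before the pairwise ones is equally unstated; it would give about 11–14% for any false pairwise rejection and about 5–6% for a herb falsely better than placebo. This stands: the figures are conditional on the any-one-suffices reading.

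**A 20–25% chance of a false superiority claim.** A reader might infer this from the six-test figure. The document does not support it. That figure also counts rejections in which the herb is worse than placebo, which nobody would report as superiority. For herb better than placebo the range is 10–13%.

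**Counting Group 1 versus Group 2 as well.** The Discussion's interest in an added effect of the blood-activating herbs suggests this comparison, and including it would raise the two-directional figure to 25–32%. It is not stated as a formal hypothesis and was not sized, so it is left out of the main figure.

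**Chance findings among the mechanism markers.** The article says "Mechanism will be assessed between mechanism index and primary outcomes by ANCOVA and regression analysis", and 27 named markers by three outcomes would be 81 tests, with 81 × 0.05 ≈ 4 false positives expected. One test per pair is not specified, however, and the article already describes this work as exploring mechanism. It is a side issue.

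**Conclusion.** The point holds. The article combines three unranked primary outcomes, two herb-versus-placebo comparisons and one unadjusted two-sided 0.05, and does not define success. If any one significant primary result may support a claim, the chance of at least one false rejection is about 19–25% in both directions together, and about 10–13% for herb better than placebo against a nominal 2.5%.

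These figures rest on an inferred decision rule, assumed outcome correlations of 0.7 down to 0, and no true effect in any arm. At a correlation of 0.9 the two-directional figure would be about 15%. The excess from having two comparisons, about 9% in place of 5% for a single outcome, does not depend on the outcome correlation.

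**What to change.** Before unblinding, amend the protocol as follows.

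1. The sponsor chooses one of two success rules. Either name one lead primary outcome (attack frequency at week 12 is an example; the article ranks none), with the other two tested after it in fixed sequence; or state that all three must be significant for a herb arm to succeed.
2. Test Group 1 versus placebo and Group 2 versus placebo by Holm, or in a stated fixed order, at an overall two-sided 0.05. If Holm is combined with a lead outcome, write down when testing moves on, for example only after both comparisons on the lead outcome are significant.
3. Report Group 1 versus Group 2 as an estimate with its confidence interval, and the mechanism marker results as exploratory.

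**Cost.** Demoting two declared primary outcomes, or adding a success rule, is a protocol and registry amendment in a trial that was already recruiting. It is more than a change of analysis wording. It also leaves fewer routes to a positive claim; requiring all three outcomes is the stricter choice.

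On the article's response rates, Holm or fixed order costs Group 2 less than one percentage point of power (about 83% against 84%, with 68 evaluable per arm). That figure does not carry over to the three primary outcomes, because the document gives no effect size or variance for them and their power cannot be computed from it.

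### For score outcomes, including the primary SAQ dimension, the plan states two overlapping efficacy tests and does not say which one decides

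*Protocol article*

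**What the plan says.** The Statistical analysis section of the protocol article gives two rules in consecutive sentences. The first is general: "Comparisons between groups will be conducted by using an analysis of covariance (ANCOVA) with baseline as covariate". It is not limited to particular outcomes and gives no time point. The second carries the efficacy label: "For efficacy analysis, changes from baseline to endpoint of treatment in scores will be tested with repeated measure analysis of variance (ANOVA". It is limited to scores, names no covariate, and does not say which term of the model is the test.

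The sentence after these gives within-group differences their own tests: a paired t-test, or the "Wilcoxon signed-rank test for non-normally distributed data". Significance is two-sided at 0.05.

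The Efficacy outcomes section lists three primary outcomes: attack frequency, nitroglycerin dosage and the body limited dimension of the SAQ. Only the last is a score. The schedule is "one visit each in week 0, week 4, week 12 and week 14". Treatment lasts 12 weeks, and week 14 ends the follow-up.

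**The concern.** The SAQ primary outcome meets the description in both sentences. ANCOVA estimates the group difference given baseline. An analysis of change with no covariate estimates the difference in mean change. The two have different standard errors and, whenever the arms differ by chance at baseline, different estimates. Nothing marks either one as primary, supportive or a sensitivity analysis.

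Two things are at stake. First, two admissible P-values for one primary outcome leave room to report the better one. Second, if the sentence carrying the efficacy label is taken as decisive, the trial discards precision that its own baseline measurement would provide.

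**Working it through.** **Inputs from the protocol article.** Sample size calculation section: 80 patients per group, 15% dropout, alpha 0.05 two-sided, power 80%. Endpoint outcomes section: visits at weeks 0, 4, 12 and 14. No standard deviation and no baseline/post correlation r is given, so r is an assumption, shown over a range.

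**The plan's own figure.** The sizing uses response rates and a chi-square test, with n = [1.960·√(2p̄q̄) + 0.842·√(p₁q₁ + p₂q₂)]² / (p₁ − p₂)².
- 88.5% vs 60%: 36 per group (stated 37).
- 82.5% vs 60%: 63 per group (stated 64).
- Dropout: 64/0.85 gives 76, so the stated 80 is a generous rounding.

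The stated figures are reproduced within one patient before dropout. Neither ANCOVA nor repeated-measures ANOVA is the test the trial was sized for. The only figure carried forward is the number of completers: 80 × 0.85 = 68 per arm.

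**Precision of the two methods.** With equal standard deviations σ at baseline and week 12:
- Variance of change: 2(1 − r)σ².
- Residual variance in ANCOVA: (1 − r²)σ².
- Ratio: 2(1 − r)/[(1 − r)(1 + r)] = 2/(1 + r).

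If ANCOVA has 80% power, change-score power is Φ[(1.960 + 0.842)/√ratio − 1.960]. At r = 0.5, for example, 2.802/√1.333 − 1.960 = 0.466, and Φ(0.466) = 0.68.

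| r | Ratio 2/(1 + r) | Extra patients | Change-score power if ANCOVA has 80% |
|---|---|---|---|
| 0.3 | 1.54 | 54% | 62% |
| 0.5 | 1.33 | 33% | 68% |
| 0.7 | 1.18 | 18% | 73% |
| 0.9 | 1.05 | 5% | 78% |

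**Simulation.** Normal data, 68 per arm, one active arm against placebo, 40,000 trials per setting:

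| r | ANCOVA power | Change-score power | Tests disagree on significance | Type I error if either test counts |
|---|---|---|---|---|
| 0.3 | 79.2% | 61.1% | 23.2% | 7.6% |
| 0.5 | 78.8% | 67.1% | 16.7% | 7.4% |
| 0.7 | 78.9% | 72.6% | 11.2% | 7.0% |

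The disagreement column is for trials with a true effect. With no effect, each test alone holds about 5%.

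**Repeated-measures form.** With weeks 0 and 12 only, the group-by-time test is the same as the change-score test. With weeks 0, 4 and 12, equal correlations between visits and an assumed half effect at week 4, power at r = 0.3, 0.5 and 0.7 was 50%, 56% and 63% for the group-by-time term. It was 45%, 32% and 19% for the group main effect. ANCOVA at week 12 had 78% to 80% on the same data. The half effect is an assumption, so these figures show direction only.

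**The case against.** **The sentences may be complementary.** ANCOVA could serve the group contrast and repeated measures the course over time. The second sentence does not say that it compares groups, and it does not exclude a covariate. The last part stands: that the analysis is unadjusted is inferred from the absence of a covariate, directly after a sentence that names one. The time-course reading is weak, because the sentence claims the efficacy analysis and within-group change has its own tests.

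**A statistical analysis plan could settle it.** None is shown, and what the article merely leaves out is not at issue. Here the article prescribes two methods for the same primary outcome, so a later plan would have to demote one of them.

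**The loss depends on r.** This is true. It is small near 0.9, and 2/(1 + r) describes a two-point change score, not every repeated-measures model.

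A reader might also infer more than the text supports:
- *That both methods apply to skewed attack counts and nitroglycerin amounts.* The repeated-measures sentence is limited to scores; only the ANCOVA sentence reaches those two outcomes.
- *That normal-theory analysis of those outcomes is invalid.* The documents say nothing about skewness or zeros. With simulated counts of assumed mean 6 and skewness of about 3 to 5, ANCOVA kept its type I error at 4.4% to 5.0%. The issue there is efficiency, and the choice of a transform or count model can be left to the analysis plan.
- *That week 14 dilutes the effect.* The sentence runs to the end of treatment, which points to week 12.

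**Conclusion.** The point holds for score outcomes, the SAQ body limited dimension being the primary one. Two overlapping between-group analyses are fixed, one with baseline adjustment and one with none stated, and neither is designated. Under equal standard deviations, change from baseline is less precise than ANCOVA at any correlation below 1. The cost is 54% to 18% more patients at r = 0.3 to 0.7 and about 5% at 0.9. Choosing between the two tests after seeing the results takes the type I error to about 7.0% to 7.6% for a single contrast of one outcome. The sizes rest on assumed correlations and, in the simulations, on normal data with 68 completers per arm. Confidence is high that the two sentences overlap and moderate on the size of the consequence. Each test alone keeps its nominal error, so this is a problem of designation and efficiency.

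**What to change.** Name one primary analysis for each primary outcome: the between-group contrast at week 12, baseline as covariate, all three arms in one model. This can be ANCOVA, or a mixed model with baseline as covariate that also uses week 4. Delete the repeated-measures ANOVA on change or label it supportive. If it is kept, state the visits it includes, the term tested and any covariates.

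Optionally, say how non-normal attack counts and nitroglycerin amounts would be handled, for example by a log or rank transform or a count model. That would serve efficiency and is not required for validity.

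The cost is a few sentences in the protocol or analysis plan, with no added patients, visits or measurements. The Trial status section reports recruitment as ongoing at submission. The change should be made and dated before unblinding.
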